## Abstract

**Background:**

Insomnia and sleep disturbances are common in pregnancy and have potentially significant consequences for both maternal and infant health. There is limited research examining the effectiveness of cognitive behavioral therapy for insomnia (CBT-I) during pregnancy. With increased distress and limited access to services during the COVID-19 pandemic, there is also an unprecedented need for telehealth delivery of treatment programs for pregnant women. The aims of this trial are to evaluate the impact of the Sleeping for Two adaptation of CBT-I in pregnancy (in-person or telehealth) versus treatment as usual (TAU) in reducing symptoms of insomnia (primary outcome), as well as increasing gestational length and reducing symptoms of depression (secondary outcomes).

**Methods:**

A two-arm, single-blinded, parallel group randomized controlled trial (RCT) design with repeated measures will be used to evaluate the impact of CBT-I compared to TAU among a sample of 62 pregnant women, enrolled between 12 and 28 weeks of gestation, who self-identify as experiencing insomnia. Five weekly individual sessions of CBT-I will be delivered in person or via telehealth depending on physical distancing guidelines. Assessment of insomnia diagnosis by structured interview, self-reported insomnia symptom severity and sleep problems, and sleep quantity and quality as measured by a daily diary and actigraphy will occur at 12–28 weeks of pregnancy (T1), 1 week post-treatment (T2), and 6 months postpartum (T3).

**Discussion:**

CBT-I delivered in pregnancy has the potential to reduce symptoms of insomnia and depression and could lead to reduced risk of preterm birth, all of which can minimize risk of negative maternal and child health and developmental consequences in the short (e.g., infant death) and long terms (e.g., developmental delays). This RCT builds on a successful open pilot trial conducted by our team and will provide further evaluation of a novel evidence-based treatment for pregnancy-related insomnia, which can be widely disseminated and used to treat individuals that are most in need of intervention. Findings will enhance understanding of pregnancy-related sleep problems, as well as means by which to improve the health and sleep of mothers and their children.

**Trial registration:**

ClinicalTrials.gov NCT03918057. Registered on 17 April 2019.

## Administrative information

Note: the numbers in curly brackets in this protocol refer to SPIRIT checklist item numbers. The order of the items has been modified to group similar items (see http://www.equator-network.org/reporting-guidelines/spirit-2013-statement-defining-standard-protocol-items-for-clinical-trials/).

Unfortunately, insomnia and poor sleep quality during pregnancy have serious consequences for both maternal and child health, including associations with shorter gestational age (i.e., preterm birth) [13–18]. In turn, these poor birth outcomes confer long-term infant and child health risks [19–21]. Symptoms of insomnia in pregnant and non-pregnant populations are a robust predictor of increased risk of developing symptoms of depression [22–28]. In the first analysis of sleep trajectories during pregnancy, our research team showed that trajectories characterized by consistently poor sleep quality in the perinatal period or in the third trimester of pregnancy were associated with a 10- to 20-fold increased risk of postpartum depression (PPD), even after controlling for robust predictors such as depression in pregnancy and socioeconomic status [29]. Some research has also shown sleep disturbances predate increases in anxiety during pregnancy [27, 30]. Without intervention, symptoms of depression and anxiety are relatively stable from pregnancy to the postpartum period [31], and associated with serious long-term negative consequences for child development across physical, social, emotional and cognitive domains [32–35]. Interventions targeting antenatal sleep may prevent the direct consequences of poor sleep on maternal-child health and also prevent or minimize the myriad negative child developmental consequences associated with PPD and postpartum anxiety.

Poor sleep quality and maladaptive maternal cognitions about sleep have been shown to predict poor infant sleep [36, 37]. Poor infant sleep-wake organization contributes to child developmental outcomes, such that unconsolidated and short sleep in infancy and childhood can significantly interfere with attention regulation, concentration, and cognitive, social and behavioural development [38–49]. The largest changes in sleep maturation are observed in the first six months of life, after which point changes continue to occur but at a more moderate pace [50, 51]. At six months of age, sleep has consolidated to the point where many infants are considered to be “sleeping through the night” [50–53]. However, 20-30% of typically developing infants continue to experience multiple extended nighttime awakenings [54, 55]. Optimizing sleep in an at-risk group of mothers suffering from antenatal insomnia is an important and understudied means of potentially improving both maternal health and child development.

The prevalence and consequences of untreated antenatal insomnia for maternal mental health and infant development highlight the need for evidence-based treatment for insomnia during pregnancy. Additionally, patient-oriented approaches to research priority-setting (from conception to age two) show that parents, clinicians, and policymakers rate optimizing sleep quality as a top research priority [56]. Use of pharmacotherapy in pregnancy may improve sleep quality [57]; however, best practice guidelines advise against the use of the majority of sedative sleep medications in pregnancy due to potential teratogenicity [58]. Additionally, pregnant women are reluctant to take prescription medications due to their perception of risk for the developing fetus [59, 60]. In two studies of treatment preferences for insomnia during pregnancy, our team found that when presented with descriptions of pharmacotherapy versus cognitive behavioural therapy for insomnia (CBT-I), pregnant women and their partners rated CBT-I as the more credible and preferable treatment [61, 62]. Matching patients to their preferred treatment modality increases adherence and treatment response [63].

CBT-I is an evidence-based psychotherapeutic intervention that combines cognitive and behavioural principles. Psychoeducation about thoughts that contribute to the maintenance of sleep problems is provided, and instruction in behavioural techniques is offered to help decrease sleep onset latency and promote sleep maintenance. CBT-I is an effective treatment for insomnia, with short-term efficacy equivalent to medication and long-term results showing that it outperforms medication in improving sleep, while also conferring a secondary benefit of reducing symptoms of depression [64–67]. In fact, CBT-I, not sedative medication, is the current gold standard for treatment of insomnia (American Academy of Sleep Medicine) [68]. However, pregnant women have historically been excluded from intervention research—and insomnia treatment is no exception—which prompted calls for further development of interventions to treat insomnia in pregnancy and the postpartum period [69].

There have been four studies to date [70–73] examining the effectiveness of in-person or digital CBT-I specifically in pregnancy, all showing positive results in favour of active intervention. Following the ORBIT model [74, 75], our research team conducted a Phase II open pilot trial of CBT-I for pregnant women with insomnia, demonstrating that it was effective in reducing both subjective symptoms of insomnia and improving objective indices of sleep quality [70]. Another research group conducted a multi-site randomized controlled trial (RCT) of CBT-I with an ethnically diverse sample of treatment naive women [71]. Results indicated reductions in insomnia severity, self-reported total wake time, and symptoms of depression. Two RCTs have examined the efficacy of digital CBT-I in pregnancy delivered online, with results indicating that a digital CBT-I program Sleepio (Big Health Inc.) was associated with reductions in insomnia severity and improvements in sleep duration and quality [72, 73].

With limited access to in-person services and increased fear of threat to the health of their baby during the COVID-19 pandemic [6], there is an unprecedented need for telehealth delivery of programs for pregnant women. Telehealth refers to the provision of health care services using technological modalities instead of, or in addition to, in-person methods, and include behavioural and/or mental health care (e.g., therapy using the phone, diagnostic interviews via videoconferencing, apps to track mood states, and email consultations) [76]. Telehealth adaptations of CBT-I also address barriers to accessing treatment reported by pregnant women, such as transportation, childcare and/or work hours [77–80]. The COVID-19 pandemic has served as a catalyst for the implementation of telehealth mental health care services [81]. Indeed, our team launched a Phase III randomized controlled trial of CBT-I for pregnant women comprising five individual in-person therapy sessions, however, when COVID-19 was declared a pandemic and physical distancing measures were enacted, we amended the protocol to deliver the intervention by telehealth (i.e., videoconferencing). This presents the unique opportunity to be the first study to investigate the efficacy of CBT-I delivered via telehealth during pregnancy.

## Objectives {7}

The primary aim of this study is to conduct a phase III RCT to evaluate the impact of CBT-I for treatment of insomnia experienced in pregnancy compared to a treatment as usual (TAU) control group. We hypothesize that participants who receive the CBT-I intervention, delivered in person or via telehealth, will report fewer insomnia symptoms and have improved objectively assessed sleep measured at 1 week post-treatment (T2), and that treatment gains will be maintained at 6 months postpartum (T3).

The secondary aims of the trial are to determine whether CBT-I versus TAU is associated with: (1) reduced symptoms of depression at T2 and T3; (2) and a lower risk of preterm birth as assessed by gestational length. We hypothesize that participants who receive CBT-I (versus TAU) will report fewer depressive symptoms at 1 week post-treatment (T2) and that symptom reduction will be maintained at 6 months postpartum (T3). We also hypothesize that CBT-I versus TAU will be associated with a lower risk of preterm birth (confirmed by public health records after delivery, between T2 and T3).

Exploratory research questions will investigate whether CBT-I delivered in pregnancy is associated with: (1) fewer symptoms of maternal anxiety at T2 and T3; and (2) better infant sleep at 6 months postpartum (T3). We hypothesize that mothers who receive CBT-I compared to the TAU group will report lower anxiety at 1 week post-treatment (T2) and that treatment gains will be maintained at 6 months postpartum (T3). We also hypothesize that the infants of mothers who receive CBT-I will demonstrate better sleep at 6 months. Additionally, we expect CBT-I in pregnancy delivered via telehealth will be associated with the same treatment response outcomes as in-person therapy, given both use the same protocol for model fidelity (i.e., manualized, supervision, monitoring).

## Trial design {8}

A two-arm, single-blinded, parallel group randomized controlled trial (RCT) design with repeated measures will be used to evaluate the impact of CBT-I delivered in person or via telehealth for treatment of insomnia experienced in pregnancy compared to the TAU control group. Assessments will occur at baseline, between 12 and 28 weeks of pregnancy (T1), 1 week post-treatment (T2), and 6 months postpartum (T3).

This trial adheres to the Standard Protocol Items: Recommendations for Intervention Trials (SPIRIT) guidelines [82] and was registered with ClinicalTrials.gov (NCT03918057). All procedures were performed in accordance with the University of Calgary Conjoint Health Research Ethics Board (REB19-0465) and the 1964 Helsinki declaration and its later amendments. All participants provided informed consent prior to enrollment in the study.

## Methods: participants, interventions, and outcomes

### Study setting {9}

Participants will be recruited from Alberta, Canada. Data will be collected in-person at the University of Calgary or online through Qualtrics® survey software (SAP America Inc.), which is hosted on the university’s secure server. Therapy was being conducted in-person at the University of Calgary Psychology Clinic prior to COVID-19 being declared a pandemic and then via telehealth after physical distancing measures were implemented, using the clinic’s securely hosted Jane App (Jane Software Inc.) online platform for virtual health appointments.

### Eligibility criteria {10}

#### Inclusion and exclusion criteria

English speaking women from Alberta, over the age of 18, who are 12–28 weeks of gestation, and who report experiencing insomnia in pregnancy will be eligible. Exclusion criteria include the following: (1) experiencing symptoms of sleep disorders other than insomnia (i.e., restless legs syndrome, sleep-disordered breathing); (2) having a lifetime diagnosis of bipolar or psychotic disorder; (3) currently taking prescribed medications for sleep problems or taking medications known to impact sleep; (4) smoking, drinking alcohol, or drug abuse during pregnancy; (5) pregnant with multiples; and (6) diagnosis of chronic pain.

#### Screening and enrollment

After informed consent is obtained, participants answer a series of questions during a phone screen; those above the cut-off score of 10 on the Insomnia Severity Index (ISI), which yields 86.1% sensitivity and 87.7% specificity for detecting insomnia in a community sample [83], will be invited to complete a subsequent baseline assessment, in the lab or via online videoconference, to determine further eligibility for the study. Insomnia diagnosis will be confirmed, and screening for restless legs syndrome (RLS) and sleep-disordered breathing (SDB) will be conducted using the Structured Clinical Interview for DSM-5 Sleep Disorders (SCISD) [84]. Women whose scores are suggestive of a sleep disorder other than insomnia will be referred to their primary care provider for further assessment. Participants will also be administered the Diagnostic Interview for Anxiety, Mood, and OCD and Related Neuropsychiatric Disorders (DIAMOND) [85], to assess if any other exclusionary criteria are present. Diagnoses will be confirmed in consensus conferences with a licensed, doctoral level clinical psychologist.

### Who will take informed consent? {26a}

Prospective participants who agree to be involved in the study will meet with a member of the research team, who will explain the study procedures in full detail and obtain written consent.

### Additional consent provisions for collection and use of participant data and biological specimens {26b}

Not applicable.

## Interventions

### Explanation for the choice of comparators {6b}

The control arm of the study is designed to account for the potential effects of time and regular care on the change in insomnia symptoms [74]. A control group will be used to test whether CBT-I will result in improvement in study outcomes (sleep, mood) compared to treatment as usual (TAU). At the end of their participation (completion of follow-up visit), TAU/control participants will be offered the CBT-I intervention, which has been successfully delivered in the postpartum [86].

### Intervention description {11a}

The Sleeping for Two adaptation for CBT-I in pregnancy consists of five weekly 60-minute individual therapy sessions of CBT-I. Participants are asked to use a daily sleep diary for self-monitoring and receive a manual containing readings summarizing the material being taught in-session. The manual was adapted from a treatment protocol previously validated for oncology patients with comorbid insomnia [87]. In adapting the CBT-I protocol for use with pregnant women, we followed steps outlined in the ORBIT Model [74, 75] for developing behavioural therapies to treat or prevent chronic diseases and enhance health-promoting behaviours (e.g., sleep): Phase I (i.e., defined the question), Phase IIa (i.e., created a fixed treatment package; see Appendix A for session structure), Phase IIb (i.e., pilot tested the intervention), and Phase III (i.e., a randomized controlled trial; RCT). This manuscript represents Phase III.

During this five-session intervention, patients are familiarized with the self-management approach for insomnia (e.g., active vs. passive coping strategies). First, patients are oriented to CBT-I (e.g., use of daily sleep diaries) and set individualized treatment goals (Session 1). The remaining sessions consist of weekly review of sleep diaries, psychoeducation about sleep and sleep consolidation (Session 2), stimulus control (Session 3), cognitive strategies to examine attitudes and beliefs about sleep (Session 4), and problem-solving to cope with sleep disturbances and relapse prevention (Session 5). In the final session, participants are also provided information on infant sleep and the importance of mutual regulation, which was adapted from evidenced-based behavioural-education programs [88] and consultation with infant sleep experts. A licensed clinical

psychologist with extensive training in CBT-I will supervise the administration of the intervention ([name]).

The control group will receive regular obstetric care provided according to the needs and current regime of the patient. The amount of contact with health care professionals outside of the study will be recorded, coded, and reported, as well as any treatment for insomnia (e.g., medication use, searching the internet for techniques to improve sleep) that the patient engages in. After study completion, TAU participants will be offered the CBT-I intervention, which has been successfully delivered in the postpartum [86].

### Criteria for discontinuing or modifying allocated interventions {11b}

Participants who do not appear for the first or second session are not able to continue receiving treatment (but can remain in the study). In accordance with the College of Alberta Psychologists Practice Guidelines for Telepsychology Services, therapists may decide to terminate telehealth services if they deem it inappropriate for the client to continue therapy through videoconferencing sessions (e.g., the participant cannot ensure privacy and confidentiality is maintained through availability of a secure space and stable Internet connection, or environmental factors interfere with their engagement). In this case, the investigators will provide in-person care or a referral to another provider or clinic, if necessary.

### Strategies to improve adherence to interventions {11c}

Scheduled study-related reminders will be sent to participants through the Jane App service. Sleep diaries and homework for the past week will be reviewed at the beginning of each session. Therapists will also be instructed to use several strategies to promote treatment adherence, including 5-step problem-solving, identifying barriers and resistance, reframing, cognitive restructuring, and reminding patients of the goals they set at the beginning of treatment.

### Relevant concomitant care permitted or prohibited during the trial {11d}

Potential participants who report taking prescribed medications for sleep problems will not be invited to participate in the study due to potential side effects of medication during pregnancy. Because this intervention is designed to be an adjunct to usual care in pregnancy, participants will not be excluded if they are receiving common medical and physical therapies that are not known to interfere with sleep. Participants will be permitted to receive concomitant care for unrelated mental health problems (i.e., not insomnia).

### Provisions for post-trial care {30}

At the end of their participation (completion of follow-up visit), TAU/control participants will be offered CBT-I treatment. If further treatment is deemed necessary, a referral to another provider or clinic will be made, and a list of community services will be provided.

### Outcomes {12}

The primary outcome is mean change in insomnia severity across all timepoints. The mean change in sleep quality (measured by self-report questionnaires) and sleep parameters such as onset latency, wake after sleep onset, number of awakenings, total sleep time, and sleep efficiency (measured by actigraphy and daily sleep diaries), as well as insomnia diagnosis remission, will also be evaluated.

Secondary outcomes include mean change in symptoms of depression (measured by self-report questionnaire) across all timepoints, as well as the rate of preterm birth (assessed from public health records at T3).

Exploratory outcomes include mean change in symptoms of anxiety (measured by self-report questionnaires) across all timepoints, as well as mean infant sleep problems (measured by parent-report questionnaire at T3).

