### Recruitment {15}

Participants will be recruited from Alberta, Canada, through ultrasound clinics and a low risk primary care maternity clinic, where they will be approached by a research assistant or can respond to the posted advertisements. Potential participants will also be able to self-refer through advertisements posted online (e.g., lab website and social media accounts including Facebook, Instagram, and Twitter). Those interested in participating will contact the investigators’ lab and receive additional information about the study protocols.

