#### Secondary outcomes

*Symptoms of depression* will be assessed with the Edinburgh Postpartum Depression Scale (EPDS) [105]. The EPDS consists of 10 items, and is a reliable and valid tool for identifying symptoms of depression in pregnancy and the postpartum [106]. We will also collect information about psychiatric diagnoses from the SCID-5 [107].

*Infant birth outcomes*, including information about preterm birth (e.g., gestational length), delivery type, and birth weight, will be gathered through linkage to participants’ heath records for the Alberta Perinatal Health Program.

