## Statistical methods

### Statistical methods for primary and secondary outcomes {20a}

Categorical variables will be analyzed using chi-square tests. Ordinal variables will be analyzed using nonparametric tests in addition to using Student’s *t* tests. Independent-samples*t* test, *χ*^2^ test, and Fisher’s exact test will be used to compare the groups on demographic characteristics known to influence sleep, such as age, parity, body mass index, and socioeconomic status; covariates found to differ between groups will be controlled for in subsequent analyses. Primary analyses of insomnia severity will be conducted using generalized estimated equations (GEE) and an intent-to-treat (ITT) approach. Other sleep measures including insomnia diagnosis, self-reported sleep quality, and actigraphy parameters will also be assessed using GEE. Secondary response variables including diagnosis and symptoms of depression, as well as preterm birth, will be examined. Changes in binary outcomes will be tested using GEE with a binary outcome specified.

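### The birth outcome is gestational length in one place and rate of preterm birth in another; the binary version would have very low power and fits the stated GEE for changes poorly

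*Protocol article*

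**What the plan says.** Four places in the protocol article describe the birth outcome:

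- **Abstract, Background:** a continuous outcome, "increasing gestational length and reducing symptoms of depression (secondary outcomes".
- **Objectives {7}:** a hybrid, "a lower risk of preterm birth as assessed by gestational length". The hypothesis that follows is about risk: "lower risk of preterm birth (confirmed by public health records after delivery, between T2 and T3".
- **Outcomes {12}:** a binary outcome, "as well as the rate of preterm birth (assessed from public health records at T3".
- **Secondary outcomes, under {18a}:** record linkage, "including information about preterm birth (e.g., gestational length), delivery type, and birth weight". Here gestational length is an example of the information gathered.

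No cut-off in weeks is given, and nothing says which variable is compared between arms.

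Statistical methods {20a} opens with a general chi-square rule for categorical variables. It later says that preterm birth is among the secondary variables to be examined, and then adds: "Changes in binary outcomes will be tested using GEE with a binary outcome specified". Methods for additional analyses {20b} does set a single-time-point method (ANOVA) for infant sleep, because that is measured only postpartum. Preterm birth gets no such provision.

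Sample size {14} rests on insomnia effect sizes only.

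**The concern.** Gestational length in days and a yes/no preterm indicator are different variables with different effect measures and different precision. As the article stands, either could later be reported as the pre-specified outcome, and the choice could follow the data.

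The method is also unsettled. A GEE for changes presupposes repeated measurements, and a woman delivers once. The chi-square rule could apply instead, but the text does not say so. It also says that covariates found to differ between groups will be controlled for, which a chi-square test cannot do.

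The binary version will rest on few events. The abstract and the Discussion both present lower preterm risk as a potential benefit, so a sparse result could be read as evidence for or against a benefit when it carries almost no information.

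**Working it through.** **The plan's own figure.** The plan gives no rate, effect or power for preterm birth, so there is no figure to reproduce for this outcome. Its sample size of 44 is for a medium effect (f = 0.25) over three time points. A repeated-measures ANOVA interaction, with assumed correlation 0.5, two-sided alpha 0.05 and power 0.95, gives 44 exactly. The sample size is therefore not in dispute for its own purpose.

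**Inputs**
- From Sequence generation {16a}: n = 31 per arm.
- Assumed: two-sided alpha 0.05; preterm rate p_C in TAU of 5%, 8%, 10%, 15% or 20%; CBT-I halves it, p_T = p_C/2. The document gives none of these.
- The document's pointers to the rate are mixed. Multiples and smokers are excluded, and one source is "a low risk primary care maternity clinic". But women also come through ultrasound clinics and self-referral, and the Background links insomnia to shorter gestation.

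**Formulas**
- Expected events = 31 × (p_C + p_T).
- Normal-approximation power = Φ[(d − 1.96·SE0)/SE1], where d = p_C − p_T, p̄ = (p_C + p_T)/2, SE0 = √(2p̄(1 − p̄)/31) and SE1 = √((p_C(1 − p_C) + p_T(1 − p_T))/31).
- Fisher power: the sum of binomial probabilities over all tables with p ≤ 0.05.
- Chance that at least one arm has no event = 1 − [1 − (1 − p_C)^31][1 − (1 − p_T)^31].

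**Worked case, p_C = 10%, p_T = 5%**
- Events: 31 × 0.15 = 4.65.
- SE0 = √(2 × 0.075 × 0.925/31) = 0.0669 and SE1 = √((0.09 + 0.0475)/31) = 0.0666.
- Power = Φ[(0.05 − 0.1311)/0.0666] = Φ(−1.22) = 0.11.
- Zero-event arm: 0.90^31 = 0.038 and 0.95^31 = 0.204, so 1 − 0.962 × 0.796 = 0.234.

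| TAU rate | Total events | Power, normal | Power, Fisher | At least one arm with no event | n per arm for 80% power |
|---|---|---|---|---|---|
| 5% | 2.3 | 7% | 0.2% | 57% | 906 |
| 8% | 3.7 | 10% | 1.1% | 34% | 553 |
| 10% | 4.7 | 11% | 2.1% | 23% | 435 |
| 15% | 7.0 | 15% | 5.7% | 10% | 278 |
| 20% | 9.3 | 19% | 10% | 4% | 199 |

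If CBT-I had no preterm births at all, Fisher's test would need at least 6 in TAU (5 v 0 gives p = 0.053; 6 v 0 gives p = 0.024). Power would then be 8% at a TAU rate of 10% and 32% at 15%.

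**Does GEE run on one record per woman?** With illustrative counts of 4/31 and 2/31, a binomial GEE gives the same coefficients and standard errors as logistic regression (treatment log odds ratio −0.765, SE 0.906). It runs. It fails to give a finite treatment estimate only when an arm has no event.

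**Gestational length instead.** For a two-sample t-test at 80% power, the detectable difference is about (1.96 + 0.84) × √(2/31) = 0.71 SD by normal approximation and 0.72 SD with the t distribution. With 25 per arm, after the plan's 20% attrition, it is 0.81 SD.

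**The case against.** **The definitions can largely be read together.** Gestational length may be the recorded datum and preterm birth the outcome derived from it; that reading suits the Objectives, the Outcomes section and the linkage text. This stands in part. It leaves the abstract as the clear outlier, and it supplies neither a cut-off nor the analysed variable. The difference between a timing of T3 and one between T2 and T3 can be read the same way, as delivery and later record extraction, and is not pressed.

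**The article never ties GEE to preterm birth by name.** This stands. The sentence on changes fits insomnia and depression diagnoses, which are repeated, and the chi-square rule could cover a one-off outcome. What remains is that two rules are on the page and neither is assigned, although infant sleep was given its own.

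**Stronger readings a reader might infer.** One is that GEE is impossible without repeated measures. It is not, since it reduces to logistic regression with robust standard errors; sparse cells are the obstacle. Another is that the preterm hypothesis cannot be tested at all. It can, but without useful power. A third is that low power is itself a design error. This is a secondary outcome for which the plan claims no power, so it is not.

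**Event counts rest on assumed rates, and Fisher's test is the conservative choice.** Both are true; the article names Fisher's test only for baseline comparisons. Hence the range of rates and both power figures. Normal-approximation power is still only 19% at a 20% TAU rate.

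**Conclusion.** The concern holds in a limited form. The inconsistency between the abstract, Objectives and Outcomes is in the text and needs no assumption. The mismatch between an outcome observed once and a GEE for changes is also in the text, tempered by the chi-square rule beside it.

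The size of the power problem depends on the assumed rates, two-sided alpha of 0.05 and a halving of risk. Over TAU rates of 5% to 15%, the binary comparison has about 2 to 7 events and at most about 15% power. The zero-event risk is substantial at the lower rates. No rate examined, up to 20%, gives useful power for a halving.

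This should be fixed, but it does not threaten the trial: insomnia severity and the sample size built on it are unaffected.

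**What to change.** 1. Name gestational length, from the perinatal record, as the single analysed birth outcome in the abstract, Objectives {7}, Outcomes {12} and Statistical methods {20a}.
2. Compare arms with a single-time-point method, for example linear regression with robust standard errors, and state that the GEE rule for changes does not apply to this outcome.
3. Report preterm births, with the cut-off in weeks stated, as counts per arm with an exact confidence interval for the risk difference. Label this descriptive and not a confirmatory test, and word the preterm hypothesis to match.
4. Trial status reports that recruitment finished on October 21, 2020. Settling the analysed variable now is more than an editorial change, so record it as a dated clarification before outcome data are analysed.

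No new data are needed, because the linkage already collects gestational length. The cost is that no formal claim on preterm risk can be made. The replacement is also modest: with 31 per arm it detects only a difference of about 0.7 SD with 80% power. It does give a finite, interpretable estimate however few preterm births occur.
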